### Ethical Considerations

This study was approved by the Ethics Committee of the City of Vienna (EK-23-103-0623). Further authorization for medical device investigation was obtained from the Austrian Federal Office for Safety in Health and Care (BASG; 10239778, 2023-27-10). The trial was registered at ClinicalTrials (NCT06161194, December 7, 2023). The final protocol approved by the Ethics Committee refers to version 3.3 from December 7, 2023. Recruitment was planned to begin on December 19, 2023, and will approximately be closed by November 6, 2024.

Participants will be assigned a continuous study code (THA01-THA70) to protect identifiable data. The assignment key will be locked in the study manager’s office, separate from identifiable study data.

## Results

The trial started in January 2024, and the first results are anticipated to be published by June 2025. Based on the knowledge from comparable (to some extent) studies on RTF effectiveness in motor re-education conditions, we expect that RTF-supported home exercise will tend to be more effective compared to using paper instructions for exercise guidance. This effect might be reported for all 3 hypotheses (functional deficits, quality of life, and activity questionnaires), as well as biomechanical parameters.

## Discussion

### Principal Findings

RTF-supported home exercise is expected to improve exercise execution quality and therapeutic adherence compared to using paper instructions for exercise guidance. As a consequence thereof, we anticipate superior results for the selected outcome measures in the IG.

### Limitations and Problems Anticipated

Participants might not be able to perform ramp walking or stair climbing without the use of handrails at baseline assessment. Dropouts are likely to occur, and thus, they may introduce a risk of attrition bias and, in the worst case, demand the premature termination of the study.

Concerning the use of the HHS and HOOS, subitems of these questionnaires will be interpreted cautiously in view of the limitation that they have been developed for patients with hip OA who did not undergo THA.

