#### Ramp Walking

Participants will be instructed to walk up and down the ramp at a self-selected comfortable speed between start and end marks without using the handrail. Familiarization trials will be carried out in the preparatory phase with a 10° inclination.

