#### Stair Climbing

Participants will be instructed to walk up and down the stairs at a self-selected comfortable speed with the whole foot placed on the single arrays without using the handrail. Familiarization trials will be carried out in the preparatory phase.

The examination procedure described before will be performed at baseline (t_0_) prior to the randomization and at 3 months (t_1_) and 6 months (t_2_) postsurgery. Follow-up assessments (t_1_ and t_2_) will be accompanied by a structured interview on exercise behavior and well-being. In addition, the IG will be interviewed concerning the acceptance of the RTF device and possible suggestions for improvements.

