### Statistical Analysis

Data will be inspected for outliers using boxplots. Shapiro-Wilk tests and additional graphical inspections of q-q plots will be applied to test for the normality assumption. Metric baseline characteristics will be indicated as means (SDs) and categorical baseline characteristics as frequencies (n, %). Unadjusted outcome scores will be reported as means (95% CIs). People from the same cluster tend to be more similar than those from different clusters, and the analysis must allow for this. A common enhancement is to apply a linear mixed effects model with the cluster specified as a random intercept. To model changes between baseline and follow-up, we will include baseline measurements as covariates. Following suggestions by Klar and Darlington [37], we will adjust for each participant’s baseline assessment and for the baseline cluster mean. Otherwise, no adjustments for covariates are foreseen. Treatment effects will be reported independently for follow-up t_1_ and follow-up t_2_, including unstandardized and standardized regression coefficients as effect estimates, standard errors, *t* statistics, and appropriate *P* values via the Satterthwaite degrees-of-freedom method. Between-cluster and residual variances will be reported for all outcomes. In the case of severe outliers or major violations of the normality assumption, logarithmic data transformation approaches will be explored. Outcome parameters on the ordinal scale will be analyzed descriptively and reported as medians with ranges. All descriptive statistics and corresponding numbers of subjects (n, %) will be reported, along with losses to follow-ups. Effect sizes will be calculated and reported accordingly (per protocol). In addition, the hypotheses will be analyzed according to the intention-to-treat principle (last value carried forward), providing a more conservative effect estimate [38] when missing observations introduce bias. The α value will be set to .05, and exact 2-sided *P* values will be reported. Hypotheses will be tested independently of each other. The 2-armed study design does not require post hoc tests, so no adjustment for familywise α error accumulation is needed.

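### Ramp and stair outcomes: the plan foresees missing baseline values, but its baseline-adjusted model has no rule that keeps those randomised patients in the analysis

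*Protocol article*

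**What the plan says.** All references are to the protocol article.

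- **Task rule.** Ramp walking is done "between start and end marks without using the handrail" (Ramp Walking). Stair climbing is done "with the whole foot placed on the single arrays without using the handrail" (Stair Climbing).
- **Timing.** The examination "will be performed at baseline (t_0_) prior to the randomization and at 3 months (t_1_) and 6 months (t_2_) postsurgery" (Stair Climbing). Baseline falls 4–6 weeks after surgery (Table 1, footnote b).
- **Anticipated problem.** "Participants might not be able to perform ramp walking or stair climbing without the use of handrails at baseline assessment" (Limitations and Problems Anticipated). No handling is attached to this remark.
- **Eligibility.** Patients must be able to walk without aids at baseline (Inclusion Criteria). Neither the inclusion nor the exclusion criteria mention ramps, stairs or handrails.
- **Model.** A linear mixed model with a random intercept for cluster is planned, in which "we will include baseline measurements as covariates". More exactly, "we will adjust for each participant’s baseline assessment and for the baseline cluster mean" (Statistical Analysis).
- **Missing data.** The only rule given is "intention-to-treat principle (last value carried forward"), used for the intention-to-treat analysis beside the per-protocol one.
- **Primary outcomes.** Table 4 lists three range-of-motion angles and does not say from which task each is taken.

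**The concern.** The measurement rule can leave an eligible, randomised patient without a t0 value for ramp-up, ramp-down, stair-up and stair-down walking. These are four of the nine recorded tasks. The other five are level walking, timed-up-and-go, sit-to-stand, its reverse, and squat lifting.

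The analysis model needs that t0 value twice, once as the patient's own covariate and once as part of the cluster mean. A mixed model cannot use a record with an empty covariate unless a rule fills it.

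Two things are at stake. First, patients with valid 3- and 6-month ramp and stair data would be left out of those analyses, including the one labelled intention-to-treat. Second, the results would describe only patients who could already manage the task unaided 4–6 weeks after surgery. A patient who could not do the task at t0 but could at 3 months would not contribute to the treatment estimate for that task.

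**Working it through.** **1. Can any stated rule fill the gap?** Carrying the last value forward needs an earlier value. Table 1 schedules no movement analysis before t0; before surgery there are only the Harris Hip Score and two days of activity monitoring. So nothing can be carried into t0, and the stated rule does not reach this case.

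**2. The plan's own power figure.** Inputs from Sample Size Estimation: d = 0.8, 24 per group, clusters of 3, intracluster correlation 0.05, α = .05. The test is two-sided (Statistical Analysis).

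- Design effect = 1 + (3 − 1) × 0.05 = 1.10
- Effective n per group = 24 / 1.10 = 21.8
- Power = Φ(0.8 × √(21.8 / 2) − 1.96) = Φ(0.68) = 0.752

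The stated 0.75 reproduces under the normal approximation.

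**3. Effect of losing a share f of the 48 analysed patients.** The article gives no f, so 10–30% is an assumption. Standard error ratio = 1/√(1 − f), ignoring clustering. Power uses the formula in step 2 with 24(1 − f) per group and the design effect held at 1.10.

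| f | Patients left of 48 | Per group | SE ratio | Power |
|---|---|---|---|---|
| 0% | 48 | 24.0 | 1.00 | 0.752 |
| 10% | 43 | 21.6 | 1.05 | 0.708 |
| 20% | 38 | 19.2 | 1.12 | 0.657 |
| 30% | 34 | 16.8 | 1.20 | 0.599 |

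If the average cluster size is allowed to shrink with f, power is slightly higher: 0.714, 0.669 and 0.617.

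**4. Bias or only precision?** Simulation with 16 clusters of 3, a true effect of −0.80 that is the same for everyone, and failure at t0 more likely in more impaired patients. The analysis was least squares adjusted for the individual baseline. Entries are mean estimate (SD).

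| f | Patients without t0 omitted | All kept (mean fill plus indicator) |
|---|---|---|
| 10% | −0.798 (0.279) | −0.800 (0.269) |
| 20% | −0.802 (0.289) | −0.801 (0.268) |
| 30% | −0.807 (0.316) | −0.808 (0.271) |

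Omission leaves the estimate unbiased and widens its spread by 0.279/0.269 = 1.04 to 0.316/0.271 = 1.17. This is a little less than the simple formula gives.

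**5. If the effect depends on impairment.** With an assumed slope of 0.3, so that more impaired patients gain more, the estimate after omission is −0.75, −0.69 and −0.67 at 10%, 20% and 30%. Keeping everyone gives −0.79 to −0.81. The former is then an estimate for the fitter patients. Nothing in the article supports a particular slope, so this shows only the direction.

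**6. The cluster mean.** Clusters have 2–5 patients (Recruitment). In a cluster of 3, one missing t0 value leaves the mean resting on two patients. In a cluster of 2, the mean equals the remaining patient's own value. A further simulation of the proposed rule, again with 16 clusters of 3 and 10–30% missing, found no bias and an SD of 0.24–0.29, against 0.25–0.33 with omission.

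**The case against.** The strongest reply is that the article nowhere says such patients are dropped. It condenses a fuller protocol, and the handling of missing covariates is commonly left to an analysis plan. It is true that omission follows from the model and is not a stated rule. But the article itself names the problem, fixes the model and gives a missing-data rule, and that rule does not cover the problem it foresaw. This goes beyond an unwritten detail.

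Four further objections stand and limit the point:

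- The article says participants *might* be unable to do the tasks. It does not predict that they will be, and gives no rate.
- Only ramp and stair outcomes are subject to the handrail condition. The other five tasks and the questionnaires are not.
- Failure at t0 comes before allocation and cannot depend on arm.
- The criteria already require walking without aids and exclude delayed healing and severe contralateral osteoarthritis. That those affected are the most impaired is plausible but not stated.

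It can also be objected that mean filling makes the clusters of affected patients look better at baseline than they were. That is so, but in the simulation of the proposed rule it did not bias the treatment estimate. Finally, recruitment was due to close around November 2024, so a new baseline data field may come late for many patients. The analysis rule can still be fixed.

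**Conclusion.** The gap is real and confined to ramp-up, ramp-down, stair-up and stair-down outcomes. Run as written, the models would omit randomised patients who have follow-up data but no t0 value. The cost is a standard error about 5–20% larger if 10–30% are affected, and results that apply only to patients able to do the task at t0. The size rests on the assumed share. The omission rests on fitting the stated model without an added rule.

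A reader might infer that the comparison of arms is biased by attrition, or that the primary analysis is compromised. The documents support neither. The loss precedes allocation, and the estimate shifts only if the effect varies with impairment. Table 4 attaches no task to the primary angles, so whether the primary analysis is affected cannot be determined.

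**What to change.** Add to Statistical Analysis: for ramp and stair outcomes, a missing t0 value is replaced by the t0 mean of that task pooled over both arms, with an indicator for missing baseline in the model. The baseline cluster mean is computed from the completed values, so that every patient with follow-up data on the task stays in.

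Record inability to do a task without the handrail as a data value. Report by arm how many could do each task unaided at t0, t1 and t2, so that a change from unable to able is visible. Naming the task behind each primary angle would settle how far the point reaches.

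The cost is one data field, a sentence or two in the analysis text and one descriptive table. The downside is somewhat weaker baseline adjustment for the affected patients and their clusters. The follow-up measurements are already scheduled.

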### Conclusion

To the best of our knowledge, this is the first study to investigate the effect of RTF-supported home exercise following THA. Hypotheses will be tested not only using PROM data but also by means of objectively measured kinematic and kinetic data. Based on the results, the knowledge of more effective rehabilitation pathways after THA and the functional performance of patients 6 months postsurgery will be improved.

## Appendix

Multimedia Appendix 1 Translated health check and interview protocols.

Multimedia Appendix 2 Translated home exercise instructions and exercise overview.

Multimedia Appendix 3 Funding approval and peer review comments (translated version).

## Abbreviations

3DMA: three-dimensional movement analysis
ADL: activity of daily living
CERT: Consensus on Exercise Reporting Template
CG: control group
DOWN: ramp-down walking
HHS: Harris Hip Score
HOOS: Hip Osteoarthritis Outcome Score
IG: intervention group
IPAQ-SF: International Physical Activity Questionnaire –Short Form
KOOS: Knee Injury and Osteoarthritis Outcome Score
LAN: local area network
LW: level walking
NRS-10: 10-item Numeric Rating Scale
OA: osteoarthritis
PROM: patient-reported outcome measure
RoM: range of motion
RTF: real-time feedback
SDOWN: stair-down climbing
SF-12: 12-item Short Form Health Survey
SLS: single-leg stance
SQL: squat lifting
STS: sit to stand
STSr: sit to stand reverse
SUP: stair-up climbing
THA: total hip arthroplasty
TuG: timed up and go
UP: ramp-up walking
